#### MMSE

2.13.4

The MMSE is a widely recognized and extensively utilized screening instrument for the assessment of cognitive impairment. This 30-point questionnaire provides a comprehensive evaluation of an individual’s cognitive capacities, encompassing a diverse array of functions such as orientation, memory, attention, language, and visual–spatial skills. A score of 24 or higher is generally considered within the normal range, whereas a score falling below this threshold may serve as an indicator of potential cognitive impairment. The MMSE takes around 10–15 min to administer and is performed by a healthcare professional. The MMSE has limitations, such as being influenced by education level, age, and language factors. We shall employ the MMSE in tandem with additional assessments, such as the EEG, to facilitate a more comprehensive evaluation of cognitive function (53). We will explore the impact of changes in cognitive function on motor function through variations in MMSE scores and FMA-UE scores.

#### MBI

2.13.5

The MBI score is used to assess the ability to perform activities of daily living (54), including 10 functions, urination control, modification, toilet use, eating, bed chair transfer, bathing, walking, dressing and walking up and down stairs. Full score = 100 points. Higher scores indicate better independence, and lower scores indicate stronger dependence (55). The MBI score and the FMA-UE score complement each other, reflecting the patient’s recovery status from different dimensions, which can intuitively reflect the clinical efficacy of ES.

### Data statement

2.14

#### Plans for assessment and collection of outcomes

2.14.1

Scale assessments will be executed by qualified rehabilitation physicians in collaboration with researchers (S1, S2, S3, S4). To improve the reliability of the findings, specific tests will be administered three times, with the results subsequently averaged. EEG recordings will be collected by the same investigator employing uniform equipment and settings to ensure consistency and repeatability across assessments. Furthermore, the data from each participant will be subjected to validity checks to verify completeness.

#### Plans for collection, laboratory evaluation and storage of biological specimens for genetic or molecular analysis in this trial/future use

2.14.2

There will be no biological specimens collected during the entire trial.

#### Data retention

2.14.3

Throughout the study, participants’ personal information will be safeguarded with the utmost confidentiality and will be accessible exclusively to authorized personnel. Each participant will receive a unique trial identification number, and their information will be securely stored within a password-protected database at the clinical trial center. Upon the conclusion of the clinical trial, all data pertaining to participants will be anonymized prior to analysis. The project will strictly comply with all relevant laws and regulations, retaining comprehensive documentation related to the clinical trial—including the trial protocol, approval documents from the Ethics Committee, summary reports, case report forms, contracts, records of serious adverse reactions and events, third-party records, and original trial documents—for a minimum of 3 years after the trial’s completion. Clinical data in paper format will be securely stored in a locked filing cabinet, while electronic data captured directly from source files will be housed on a password-protected computer with a unique access code. All research data will be subjected to statistical analysis and will only be published in a scientific paper following the acquisition of informed consent from participants, who will be queried prior to enrollment regarding their permission to disclose research data in publication (excluding details concerning disease onset, age, and gender).

#### Availability of data and materials

2.14.4

The principal investigators, [name], [name] and [name], will have access to the final trial dataset. Data can be provided to researchers upon request, subject to a review of privacy. Requests for data can be sent to the corresponding author by email.

### Statistical methods

2.15

#### Statistical methods for primary and secondary outcomes

2.15.1

We will use SPSS 23.0 statistical software for statistical analysis. The measurement data with normal distribution and homogeneity of variance will be expressed as ($\bar{x}$ ± s). If the test of variance is homogeneous and all samples follow normal distribution, the *t*-test will be selected; if the variance is uneven or a sample does not follow normal distribution, a Chi-square test will be used. If the results of ANOVA or Chi-square test are significant, further multiple comparisons will be needed, such as the SNK method, LSD method, extended *t*-test. *p* < 0.05 will be considered as statistically significant.

We will conduct Pearson’s correlation analyses to precisely quantify the relationships between changes in FMA-UE scores and changes in key EEG parameters, specifically focusing on gamma - band power and functional connectivity. These analyses will allow us to determine the extent to which electroacupuncture - induced modulation of brain activity, as reflected in EEG measures, is associated with improvements in upper limb motor function. We will also explore the relationship between changes in EEG parameters and other clinical outcomes to gain a more comprehensive understanding of the neurophysiological mechanisms underlying the effects of electroacupuncture.

We will utilize mediation and moderation analyses to dissect the complex interplay between neurological impairment (NIHSS), cognitive function (MMSE), daily living activities (MBI), and the effects of electroacupuncture on motor recovery. Specifically, we will investigate:

Whether improvements in cognitive function (MMSE) or daily living activities (MBI) mediate the relationship between electroacupuncture and gains in motor function (FMA - UE), suggesting that electroacupuncture’s effects on motor function are partially mediated by cognitive or functional improvements.Whether pre - existing levels of neurological impairment (NIHSS), cognitive function (MMSE), or daily living activities (MBI) moderate the effect of electroacupuncture on motor recovery, influencing the magnitude of the treatment response.

Moreover, we will explore potential bidirectional relationships between these variables and their combined impact on motor recovery. For instance, we will examine whether improvements in motor function (FMA - UE) may also influence cognitive function (MMSE) or daily living activities (MBI), and whether these changes in turn further enhance motor recovery. This comprehensive approach will allow us to better understand the dynamic interactions between different aspects of recovery and how they collectively contribute to the overall effectiveness of electroacupuncture.

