### Sample size

2.2

According to the previous literature, the clinically important difference of the FMA-UE scores ranged from 4.25 to 7.25 points, and the improvement of FMA-UE score of 5.25 marks a significant improvement in upper limb motor function (40). Let *α* = 0.05 (bilateral), the power at 0.80. According software, *n* = 20 can be obtained, and with a drop-out rate of around 20%, the sample size required for each group is 25 cases each. Furthermore, we will establish robust communication protocols during the study to minimize participant dropout and ensure adequate final sample size. Before the study begins, we will thoroughly explain its importance and significance to participants, fostering their comprehension and willingness to cooperate. Throughout the study, we will promptly address any questions or concerns that arise, maintaining participant engagement.

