### Inclusion/exclusion criteria

2.6

The inclusion criteria for the participants are the following:

Meet the criteria for ischemic stroke in the Chinese Guidelines for the Diagnosis and Treatment of Acute Ischemic Stroke 2023, and confirmed by CT or MRI of the head.The patient had a first-time stroke with unilateral hemiplegia.Onset ranged from 2 weeks to 3 months, and vital signs were stable.Age 45–80 years old.The patient had upper limb motor dysfunction in clinical manifestations, and FMA-UE scores in the 0–30 range.The patient can sit independently for 1 h or more.Patients who are in stable condition, conscious, have no aphasia or disorder, can understand the content of the scale, and cooperate with examination and treatment.The patient has not taken any sedative medication or muscle relaxant for 2 weeks.Informed consent to this trial, and signed written informed consent.

The exclusion criteria for the participants are the following:

Patients who are critically ill or in the acute phase and whose condition has not yet stabilized.Patients with deafness, aphasia, or severe cognitive impairment that make it difficult to communicate normally.Patients with systolic blood pressure > 180 mmHg or diastolic blood pressure > 110 mmHg, patients with severe cardiovascular, liver, kidney, blood, digestive, respiratory and other primary diseases, patients with mental illness, malignant tumors, venous thrombosis, osteoporosis, severe bleeding tendency and infection at the treatment site.Patients who are unable to recover with the study protocol or participate in other clinical experiments within 3 months or receive other related treatments in the middle of the study, which may affect the efficacy judgment of this study.Dystonia and previous motor dysfunction caused by other reasons.Pregnant and lactating women.Hemiplegia upper limb with previous trauma and bone and joint diseases.The patient is in a state of severe spasticity, i.e., modified Ashworth scale above grade IIII.The patient has pacemakers, cochlear implants and other instruments and equipment in the body.The patient has had vagus nerve surgery.The patient has sensory disturbances of the skin.

Data integrity is compromised and data will not be included in the analyses when the following:

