### Outcomes

2.13

All patients will receive baseline assessment, 1-week post-intervention assessment and 2-week post-intervention assessment. The primary outcome is the FMA-UE. The secondary indicators include EEG, NIHSS, MMSE and MBI.

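### The between-arm test of FMA-UE does not adjust for baseline, does not say whether it uses raw or change scores, and has no named primary time point

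*Protocol article*

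**What the plan says.** All places are in the protocol article.

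- **Test (2.15.1).** The t-test is conditional: "If the test of variance is homogeneous and all samples follow normal distribution". If either condition fails, a Chi-square test replaces it. ANOVA appears only as a trigger for post-hoc comparisons (SNK, LSD, extended t). The threshold is p < 0.05, tied to no visit. No baseline covariate is named for the between-arm comparison, and raw or change score is not specified. The same section plans moderation analyses by baseline NIHSS, MMSE and MBI, but these are additional to that comparison.
- **Outcome and visits (2.13).** "All patients will receive baseline assessment, 1-week post-intervention assessment and 2-week post-intervention assessment. The primary outcome is the FMA-UE". No primary time point is given. Section 2.9 places the two post-baseline assessments at the fifth and tenth sessions.
- **Population (2.6).** Entry FMA-UE is 0 to 30, and "Onset ranged from 2 weeks to 3 months".
- **Allocation (2.3).** 1:1, unstratified, 25 per arm.
- **Sample size (2.2).** Alpha and power are "0.05 (bilateral), the power at 0.80". The target is described thus: "the improvement of FMA-UE score of 5.25 marks a significant improvement in upper limb motor function". The result is 20 evaluable per group, raised to 25 for about 20% dropout. No SD is stated.
- **Status (2.1).** The trial is labelled exploratory.

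**The concern.** Baseline FMA-UE is measured in every patient and can be expected to predict FMA-UE two weeks later. Patients with entry scores anywhere from 0 to 30, and 2 weeks to 3 months from onset, will differ widely at the start. Neither stratification nor the stated test takes account of that. In a trial of 50, precision that could be had from data already collected would be lost.

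The second issue is separate. A primary outcome measured at two post-baseline visits, with no visit named, does not define a single primary test. The sample size assumes one test at two-sided 0.05. If the choice of visit stays open until results are seen, that level is not guaranteed.

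**Working it through.** **1. The plan's own figure.** The dropout step reproduces: 20 / (1 - 0.20) = 25. The 20 itself cannot be reproduced, because section 2.2 gives no SD. Back-solving for 5.25 points, two-sided 0.05, 80% power and 20 per group:

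- Normal approximation: SD = 5.25 / [sqrt(2/20) x (1.960 + 0.842)] = 5.93.
- Noncentral t, 38 df: SD = 5.77.

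Over the quoted range ("the clinically important difference of the FMA-UE scores ranged from 4.25 to 7.25 points") the t-based SD runs from 4.67 to 7.97. The protocol does not say whether the SD used was for raw or change scores.

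**2. Variance under three analyses.** Let r be the baseline-to-week-2 correlation and SD the raw-score SD, taken as equal at both times.

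- Raw score: SD^2
- Change score: 2(1 - r) SD^2
- ANCOVA: (1 - r^2) SD^2

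The ratio of ANCOVA to change score is (1 - r^2) / [2(1 - r)] = (1 + r)/2, which is never above 1. The ratio of ANCOVA to raw score is 1 - r^2, also never above 1. Neither SD nor r is in the protocol, so both are assumptions below. Power is from the noncentral t with 20 per arm and a 5.25-point difference (38 df; 37 for ANCOVA).

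**3. If 5.77 is a change-score SD.** The t-test on change has 80% power.

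| r | Variance ratio (1 + r)/2 | ANCOVA power |
|---|---|---|
| 0.5 | 0.75 | 90% |
| 0.7 | 0.85 | 86% |
| 0.8 | 0.90 | 84% |
| 0.9 | 0.95 | 82% |

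**4. If the raw SD is 8.66.** This is the SD of scores spread evenly over 0 to 30 (30 / sqrt(12) = 8.66), carried forward to week 2.

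| r | Raw t-test | Change t-test | ANCOVA |
|---|---|---|---|
| 0.7 | 46% | 67% | 74% |
| 0.8 | 46% | 84% | 88% (87.5%) |

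Against change scores, ANCOVA gains 7 points at r = 0.7 and 3.5 points at r = 0.8. Against raw scores it gains 28 to 41 points.

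**5. Two visits.** Suppose either visit could be claimed at |z| > 1.96. Family-wise error is 1 - P(|Z1| < 1.96 and |Z2| < 1.96), with (Z1, Z2) bivariate normal:

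| Correlation between visits | Family-wise error |
|---|---|
| 0 | 9.75% |
| 0.5 | 9.1% |
| 0.8 | 7.8% |
| 0.9 | 7.0% |

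With one named visit the error rate is 5%, whether or not baseline is adjusted for.

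**The case against.** **The test may be on change scores.** A reader might infer that baseline is discarded and that power would rise from 46% to 74%-88%. The text does not support this as the main reading. Section 2.15.1 does not specify the score, section 2.2 frames the target as an improvement, and the correlation analyses use changes in FMA-UE. A change score does use baseline. On that reading the gain is the smaller one in steps 3 and 4. This objection stands for size but not for direction.

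**An unadjusted comparison is valid.** This also stands. Randomisation makes the t-test unbiased, and its standard error already covers chance imbalance. A baseline gap is therefore a matter of imprecision, and the point is one of efficiency.

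**No rule says that either visit may win.** A reader might infer that FMA-UE is primary at both visits. Section 2.13 lists visits for all outcomes and names FMA-UE as primary without a time point. That leaves the visit unspecified; it does not state an either-visit rule. A fuller document may name the visit, and the trial is called exploratory. The 7.0%-9.1% is therefore conditional. Some concern remains, because section 2.2 powers the trial on a two-sided 0.05 test.

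**ANCOVA does not control the error rate.** Correct: naming one visit does that. The two remedies are separate.

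**The t-test may not be the test applied.** With entry limited to 0 to 30, non-normal scores are plausible and the Chi-square branch could be triggered. That fallback for a 0-to-66 score is a separate problem in the same sentence.

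**Conclusion.** The point holds as an efficiency improvement together with an undefined primary time point. The stated between-arm test is valid but makes less use of baseline FMA-UE than it could, and it leaves raw or change score open.

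The direction of the gain does not depend on the assumed SD; at every value of r in the tables ANCOVA has more power than either t-test. The size does depend on assumptions. It is about 2 to 10 percentage points if the implied SD of 5.77 is a change-score SD (r from 0.9 to 0.5), and about 3.5 to 7 points over change scores at a raw SD of 8.66 (r from 0.8 to 0.7). It is large only if raw scores are tested.

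The multiplicity part is weaker. Family-wise error of about 7.0%-9.1% would arise only if either visit could be claimed, which the protocol does not say, and the exploratory label softens it further.

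**What to change.** Before unblinding, amend section 2.15.1, and section 2.13 to match:

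- State one primary analysis: the between-arm difference in FMA-UE at week 2 (tenth session), by ANCOVA adjusted for baseline FMA-UE, or as the week-2 contrast of a baseline-adjusted mixed model that also uses week 1. Time since onset is an optional further covariate.
- Make FMA-UE at week 1 secondary.
- Use baseline-adjusted models for the continuous secondary outcomes as well.
- In section 2.2, give the SD behind n = 20, its source, and whether it refers to raw or change scores.

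No new data are needed: baseline FMA-UE is already collected, and time since onset has to be established for eligibility. The change is not entirely free. Recruitment began in October 2024, and section 2.19 requires a revised protocol to go for ethics approval when outcomes or analyses are modified.

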Electroacupuncture stimulation (ES), a modern treatment method that combines the advantages of acupuncture in traditional Chinese medicine with the advantages of electrical stimulation (30, 31), is selected as the stimulation method for this trial. ES produces physical stimuli at specific acupuncture points that are detected by sensory receptors, whose activation triggers peripheral sensory neurons to transmit signals to the spinal cord, where the sensory information is processed locally to elicit reflexes and is then transmitted to the brain for nervous regulation (32–34). ES as a form of sensory input, has been shown to correct abnormal brain activity by having the ability to alter the frequency, amplitude, and synchronization patterns of neural oscillations, thereby promoting brain function and aiding in neurological rehabilitation (27, 31). Studies have proved that electroacupuncture stimulation of LI11 can reduce neurological deficits and cerebral infarction volume, inhibit neuronal apoptosis and autophagy, and exert neuroprotective effects (35–37). Previous trials have proved that ES can effectively improve the motor function of the upper limbs in stroke patients (38).

Studies have proved that five major different mechanisms are involved in the beneficial effects of ES on ischemic stroke rehabilitation: Promotion of neurogenesis and cell proliferation in the central nervous system, Regulation of cerebral blood flow in the ischemic area, Anti-apoptosis in the ischemic area, Regulation of neurochemicals, Improvement of impaired long-term potentiation and memory after stroke (39). While traditional electroacupuncture protocols have demonstrated therapeutic efficacy in stroke rehabilitation, they also have limitations and do not fully consider the significance of employing specific frequencies of electrical stimulation. For instance, it remains to be determined whether 40-Hz ES can directly induce gamma oscillations in the brain and thereby harness the unique therapeutic effects of gamma oscillations in neurorehabilitation. The potential of 40-Hz ES on the rehabilitation of upper limb motor function in stroke patients is an area that warrants further investigation. The overall objective of this randomized clinical trial is to seek the clinical efficacy and mechanism of 40-Hz ES to promote upper limb motor functional rehabilitation of stroke patients from the levels of rehabilitation efficacy, neural circuit and brain network.

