#### Methods for additional analyses

2.15.3

Subgroup analyses are not planned for this study.

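### The EEG-motor link is planned as a plain Pearson correlation with no stated handling of arm, and the mediation analyses fix no visits, so a treatment shift or reverse causation could be reported as mechanism

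*Protocol article*

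**What the plan says.** The Introduction makes mechanism part of the overall aim: "to seek the clinical efficacy and mechanism of 40-Hz ES to promote upper limb motor functional rehabilitation of stroke patients".

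For the brain-motor link, section 2.15.1 names one method, Pearson "correlation analyses to precisely quantify the relationships between changes in FMA-UE scores and changes in key EEG parameters", with gamma-band power and functional connectivity as the parameters of interest. The same paragraph says what the result will be used for: "determine the extent to which electroacupuncture - induced modulation of brain activity, as reflected in EEG measures, is associated with improvements in upper limb motor function". It does not mention treatment arm, a partial correlation, or separate analysis by arm.

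Section 2.15.1 then plans mediation analyses, asking "Whether improvements in cognitive function (MMSE) or daily living activities (MBI) mediate the relationship between electroacupuncture and gains in motor function". No visit is given for mediator or outcome, and no EEG measure is listed as a mediator. The closing paragraph of the section adds the reverse direction and a further step, that motor gains "may also influence cognitive function (MMSE) or daily living activities (MBI), and whether these changes in turn further enhance motor recovery".

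On timing, section 2.13 states: "All patients will receive baseline assessment, 1-week post-intervention assessment and 2-week post-intervention assessment". Section 2.9 places the two later assessments at the fifth and tenth sessions, so there are two post-baseline visits.

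**The concern.** A correlation of two change scores across both arms combines two things: the association between patients within an arm, and the difference between arms in both means. If stimulation raises gamma power and FMA-UE through unrelated routes, the second part alone gives a positive correlation. The plan would then describe it as the link between treatment-induced brain change and motor recovery. Treatment moving both measures is what the trial hopes to see, so the artefact would arise in the scenario of most interest.

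The mediation plan has a related weakness. MMSE, MBI and FMA-UE are assessed at the same visits. If mediator and outcome come from the same visit, a mediation model cannot tell MBI driving FMA-UE from FMA-UE driving MBI. The second is plausible, because section 2.13.5 lists eating, dressing and bathing among the MBI items. At stake is the trial's mechanistic conclusion.

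**Working it through.** **Plan's own figure.** Section 2.2 gives a 5.25-point difference, two-sided alpha 0.05, power 0.80, n = 20 per group and about 20% dropout. The dropout step reproduces: 20 / (1 − 0.20) = 25. The n = 20 cannot be reproduced because no SD is stated, so I solved for it:

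- Normal approximation: d = (1.960 + 0.842) × √(2/20) = 0.886, so SD = 5.25 / 0.886 = 5.93.
- t-test: d = 0.909, so SD = 5.25 / 0.909 = 5.77.

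I use d₁ = 0.91 for FMA-UE. The document gives no effect size for gamma power, so d₂ is an assumption and is shown as a range.

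**Expected pooled correlation** with zero within-arm association and 1:1 allocation:

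r = (d₁d₂/4) / √[(1 + d₁²/4)(1 + d₂²/4)]

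For d₁ = d₂ = 0.909, d²/4 = 0.2066 and r = 0.2066 / 1.2066 = 0.171.

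**Rate of p < 0.05** (40,000 simulated trials per row, zero within-arm association, d₁ = 0.91):

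| Gamma shift d₂ (assumed) | Expected pooled r | Pooled, N = 40 | Pooled, N = 50 | Arm-adjusted, either N |
|---|---|---|---|---|
| 0 | 0 | 5% | 5% | 5% |
| 0.5 | 0.10 | 9% | 11% | 5% |
| 0.91 | 0.17 | 19% | 22% | 5% |
| 1.2 | 0.21 | 27% | 33% | 5% |
| 1.5 | 0.25 | 35% | 43% | 5% |

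If FMA-UE does not shift, the pooled rate is also about 5% whatever gamma does.

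Hand check of the 19%: Fisher's z for r = 0.171 is 0.173, and 0.173 × √37 = 1.05. The upper-tail probability beyond 1.96 − 1.05 = 0.91 is about 18%, in agreement.

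**Mediation with no true mediator effect** (3,000 simulated trials per cell; mediation declared when both arm→mediator and mediator→outcome given arm are significant; mediator and outcome at the same visit). Under reverse causation, arm→FMA-UE→MBI or MMSE, with an assumed path of 0.3 / 0.5 / 0.7:

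- N = 40: declared in 5% / 27% / 51% of trials; apparent proportion mediated about 9% / 26% / 49%.
- N = 50: declared in 8% / 33% / 59%.

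Under a shared recovery factor (assumed within-arm correlation 0.3 to 0.7, mediator shift 0.5 or 0.91 SD), it is declared in 15% to 81% of trials at N = 40 and 22% to 88% at N = 50.

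**Time order.** Mediator at week 1 and outcome at week 2 is a two-step order that the schedule supports. The chain in the last paragraph of section 2.15.1 runs from motor gain to cognition or daily living to further motor gain. That is three successive post-baseline changes, and there are only two post-baseline visits.

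**The case against.** A reader might infer that the protocol pools the arms. It does not say so. Reference to treatment-induced change would also fit an analysis within the trial group or within each arm, which would avoid the artefact. Covariates and visits are often left to an analysis plan. This stands as a limit: the inflation figures are conditional on pooling. The point survives because the article commits both to a plain correlation as its only named method and to a treatment-related reading of the result.

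It can also be said that when treatment moves both measures they are truly associated across all patients, and that the article claims only association. That is fair. Pooled and arm-adjusted correlations answer different questions, but only the second bears on whether patients with more gamma change recover more.

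A reader might infer that the design offers no time order at all. It does, between week 1 and week 2. The text leaves the visits unstated, and only the three-step chain exceeds the schedule.

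A reader might see the planned moderation by baseline NIHSS, MMSE and MBI as contradicting section 2.15.3, "Subgroup analyses are not planned for this study". The documents do not support that: a treatment-by-covariate interaction on a continuous score forms no subgroup.

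Finally, section 2.1 labels the trial exploratory, and EEG, MMSE and MBI are secondary. This lowers the weight of the point, but the wording of "correlation analyses to precisely quantify the relationships between changes in FMA-UE scores and changes in key EEG parameters" and "determine the extent to which electroacupuncture - induced modulation of brain activity, as reflected in EEG measures, is associated with improvements in upper limb motor function" goes beyond exploration.

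**Conclusion.** The concern holds in a limited form. If the arms are pooled and treatment shifts both measures, plain Pearson correlation produces a significant brain-motor association with no within-arm link in about 9% to 27% of trials at N = 40, for gamma shifts of 0.5 to 1.2 SD, against 5% with arm adjustment. A reader might take the 0.91 SD gamma shift as implied by the sample size. It is not: section 2.2 concerns FMA-UE only, and even that effect is back-solved from an unstated SD. If treatment moves one measure or neither, there is no inflation.

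Mediation without stated visits can present reverse causation as mediation in roughly 5% to 51% of trials at N = 40, depending on an assumed path strength. The three-step bidirectional chain cannot be ordered in time with this schedule.

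This should be changed because it affects a stated objective and the remedy is cheap. It does not touch the primary FMA-UE comparison.

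**What to change.** 1. Replace plain Pearson with an arm-adjusted partial correlation: regress week-2 FMA-UE on gamma change at a stated visit, arm, baseline FMA-UE and baseline gamma. If a within-arm analysis was intended, say so.
2. For mediation, fix mediators at week 1 and FMA-UE at week 2, adjusted for baseline values. Add gamma change as an exploratory mediator, since it is the pathway the Introduction proposes. Adjust for week-1 FMA-UE only as a sensitivity analysis, because doing so can remove early treatment effect.
3. Drop the directional claim in the last paragraph of section 2.15.1 ("we will examine whether improvements in motor function (FMA - UE) may also influence cognitive function (MMSE) or daily living activities (MBI" and the further step after it).
4. Reword "correlation analyses to precisely quantify the relationships between changes in FMA-UE scores and changes in key EEG parameters" and "determine the extent to which electroacupuncture - induced modulation of brain activity, as reflected in EEG measures, is associated with improvements in upper limb motor function" as exploratory association.

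Cost: wording and modest extra analysis on data already scheduled, with no change to patients, visits or sample size. The regression in item 1 fits an intercept and four terms, leaving 40 − 5 = 35 residual degrees of freedom with 40 patients. Week-1 mediators capture only early change. Neither arm adjustment nor time ordering removes confounding by spontaneous recovery within arm, and the report should say so.

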### Participant timeline

2.9

The participant timeline is shown in Figure 2. Participants who meet the screening criteria will undergo a “Baseline assessment” and complete an informed consent form and randomization. Participants in the trial group will undergo conventional rehabilitation treatment over a two-week period and complete 10 ES interventions. Control group participants will undergo conventional rehabilitation treatment over a two-week period and complete 10 sham ES interventions. Conventional rehabilitation treatment include proper limb positioning, transfer training, range of motion exercises, standing training, walking training, aerobic exercise, progressive resistance training, task-specific training, constraint-induced movement therapy, balance training, and mirror therapy (41). The 1-week post-intervention assessment will be conducted at the fifth intervention and the 2-week post-intervention assessment will be conducted at the tenth intervention.

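### MBI is planned as a mediator of the effect on FMA-UE although it is at least partly a consequence of arm recovery, so an indirect effect through MBI can appear without MBI playing any causal role

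*Protocol article*

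**What the plan says.** Section 2.15.1 lists among the mediation questions "Whether improvements in cognitive function (MMSE) or daily living activities (MBI) mediate the relationship between electroacupuncture and gains in motor function". It adds how a positive answer would be read: that electroacupuncture's "effects on motor function are partially mediated by cognitive or functional improvements".

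Section 2.13.5 lists the content of MBI as "urination control, modification, toilet use, eating, bed chair transfer, bathing, walking, dressing and walking up and down stairs". Section 2.15.1 then announces an exploration of two-way relations, including "whether improvements in motor function (FMA - UE) may also influence cognitive function (MMSE) or daily living activities (MBI", and asks whether such changes in turn feed back into motor recovery.

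On timing, section 2.13 says "All patients will receive baseline assessment, 1-week post-intervention assessment and 2-week post-intervention assessment", and section 2.9 places the two later visits at the fifth and tenth intervention. The article does not say which visit would supply the mediator and which the outcome, and it names no adjustment for earlier FMA-UE.

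**The concern.** A mediator has to lie on the path from treatment to outcome. Eating, dressing, bathing and toilet use plausibly become easier when the arm improves. If ES (electroacupuncture stimulation) improves the arm and the arm raises MBI, then a regression of FMA-UE on group and MBI gives MBI a positive coefficient, and the group difference in MBI completes an apparent indirect effect. This happens even if MBI does nothing for the arm.

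Total effect equals direct plus indirect effect, so whatever is wrongly credited to MBI is taken from the direct effect of ES on the arm. Mechanism is part of the trial's overall objective (end of section 1), and the plan fixes the causal reading of this result in advance.

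**Working it through.** **Inputs from the Protocol article (section 2.2).** Two-sided alpha 0.05, power 0.80, 20 per group before dropout, 25 after, and 5.25 points on FMA-UE ("the improvement of FMA-UE score of 5.25 marks a significant improvement in upper limb motor function"). The dropout step reproduces: 20 / (1 − 0.20) = 25. The article gives no figure for the mediation analysis.

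**Assumed inputs.** No SD is stated. If 5.25 is taken as the between-group difference, an SD of 5.85 gives n = 2 × (1.96 + 0.84)² × 5.85² / 5.25² ≈ 19.5, rounded up to 20, so 5.85 is used as the SD of FMA-UE change. Half of the effect (2.625 points) and half of the variance arise by week 1. MBI change = k × FMA-UE change + noise with SD 5. MBI has no effect on FMA-UE, so the true mediated share is 0.

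**Formula, both measures at week 2.** Path a (MBI on group) = k × 5.25. Path b (FMA-UE on MBI given group) = kσ² / (k²σ² + 25), with σ² = 5.85² = 34.22. Then

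ab / 5.25 = k²σ² / (k²σ² + 25).

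The falsely mediated share equals the share of within-group MBI-change variance that the arm drives.

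- k = 0.25: 2.14 / 27.14 = 7.9%
- k = 0.5: 8.56 / 33.56 = 25.5%
- k = 1: 34.22 / 59.22 = 57.8%
- k = 1.5: 77.00 / 102.00 = 75.5%

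At k = 1 this moves 0.578 × 5.25 = 3.03 points from the direct to the indirect effect.

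**Formula, week-1 MBI and week-2 FMA-UE.** With σ₁² = 34.22 / 2 = 17.11, the share is (2.625 / 5.25) × k²σ₁² / (k²σ₁² + 25).

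- k = 0.25: 0.5 × 1.07 / 26.07 = 2.1%
- k = 0.5: 0.5 × 4.28 / 29.28 = 7.3%
- k = 1: 0.5 × 17.11 / 42.11 = 20.3%
- k = 1.5: 0.5 × 38.50 / 63.50 = 30.3%

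**Simulation at the trial's size** (25 per group, 4,000 trials per setting). A result counts as significant when both paths have p < 0.05.

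| k | Week 2 both: median share / significant | Lagged: median share / significant | Lagged, adjusted for week-1 FMA-UE: median share / significant |
|---|---|---|---|
| 0.25 | 6% / 7% | 1% / 1% | 0% / 0.3% |
| 0.5 | 24% / 33% | 6% / 7% | 0% / 0.4% |
| 1 | 57% / 66% | 20% / 27% | 0% / 1.4% |
| 1.5 | 75% / 77% | 29% / 39% | 0% / 2.7% |

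With 20 per group, a significant result occurs in 5% to 68% of trials at the same visit and 1% to 32% lagged.

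**Second set of assumptions** (large sample, baseline FMA-UE and MBI as covariates, FMA-UE measurement error SD 0 to 2, arm driving 10%, 25%, 50% or 75% of MBI change).

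- Same visit: 9%, 23%, 48% and 73% falsely mediated.
- Lagged: 5%, 11%, 24% and 36%.
- Lagged and adjusted for week-1 FMA-UE: at most 0.18 points, or 0.18 / 5.25 = 3.5%.
- Lagged with no effect of ES on the arm by week 1: 0%.

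**The case against.** Five points can be made for the plan.

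1. **MBI is not simply an arm score.** It also covers urination control, walking and stairs. Patients have unilateral hemiplegia with FMA-UE of 0 to 30 (section 2.6), so the unaffected arm may do some of the tasks. This stands: MBI is only partly downstream, and how strongly it follows FMA-UE is unknown. With a weak link (k = 0.25) the false share is small.
2. **A zero effect of MBI on the arm is assumed, not documented.** Conventional rehabilitation in section 2.9 includes task-specific training and constraint-induced movement therapy, so a path from activity to arm recovery is conceivable. This also stands. A reader might infer that MBI cannot mediate; the documents do not show that. They show only that the planned analysis cannot tell mediation from its reverse.
3. **Direction is not the only fault.** A reader might infer that measuring MBI earlier never helps. In fact the lag reduces the bias, and the lag plus adjustment for week-1 FMA-UE nearly removes it. Visit order and covariates may be left to an analysis plan that is not shown, so their absence is not the point made here. The stated causal reading is.
4. **The reverse path is already announced.** Section 2.15.1 says "we will examine whether improvements in motor function (FMA - UE) may also influence cognitive function (MMSE) or daily living activities (MBI", and the plan deserves credit for this. But a second model in the other direction leaves the partial-mediation reading in place, and two correlated outcomes can each appear to mediate the other.
5. **The trial is exploratory (section 2.1) and the mediation reading is conditional on a positive result.** This limits the weight of the point but does not remove it.

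**Conclusion.** The point holds in this form: MBI is at least partly a consequence of arm recovery, so a positive mediation result through MBI cannot be read as mechanism in the way section 2.15.1 proposes. With the true mediated share set to 0, the median false share is about 6% to 75% at the same visit and about 1% to 29% with week-1 MBI and week-2 FMA-UE. It is near 0 once week-1 FMA-UE is adjusted for. These ranges rest on the assumed change SD of 5.85, 25 per group, half of the effect by week 1, and the arm driving about 8% to 75% of MBI change. None of these except the group size is documented.

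A false significant result is possible but not certain. The between-group comparison of FMA-UE does not use this model and is unaffected. The point concerns MBI only: MMSE is named in the same sentence, but section 2.13.4 does not describe it as scoring arm tasks.

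**What to change.** In section 2.15.1, remove MBI from the mediators of FMA-UE and delete the partial-mediation reading as far as it concerns functional improvement. Analyse MBI as a secondary outcome. If a path analysis is wanted, specify the reverse path that the section already announces: ES, then week-1 FMA-UE change, then week-2 MBI change, adjusted for baseline FMA-UE, baseline MBI and week-1 MBI.

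If MBI is kept as a mediator, use week-1 MBI with week-2 FMA-UE, adjust for baseline and week-1 FMA-UE, and report the result as descriptive only.

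The cost is a change of wording in the protocol or analysis plan. No new data or visits are needed, and the primary analysis is unchanged. The downside is that one announced exploratory analysis is dropped or reframed.
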